### Subsidiary Outcome Measures

Subsidiary outcomes will be measured. Specifically, satisfaction with the treatment program will be measured through an author developed Program Satisfaction Questionnaire, completed by parents and children following the intervention. Severity of injury will be assessed using the Injury Severity Score [ISS; [41]] and Abbreviated Injury Scale [AIS; [42]].

### Sample Size and Power Calculations

Given the limited research examining trauma-focused CBT interventions for childhood PTSD following accidental injury, calculations of power was based on existing preliminary evidence and related trials. Although research has traditionally demonstrated large effect sizes for the comparison of CBT interventions to no therapy or control conditions in the treatment of child anxiety disorders, there is less reporting of the expected effect size between two active treatments. Previous research conducted by Cobham et al. [23] demonstrated a large effect size (w = 0.50) for the comparison between family and child only intervention for childhood anxiety disorders. Thus, similar differences are anticipated in the present trial.

The study was powered on the comparison between the family-focused versus the child-focused intervention, as this comparison would require the most power whilst also allowing sufficient power to detect differences between the waitlist and active treatments. For the evaluation of diagnostic change (e.g. whether children became free of their PTSD diagnosis), and accounting for an attrition rate of approximately 20%, a sample size of approximately 140 participants in total across the three groups, waitlist, FF-CBT and CF-CBT, will provide sufficient power to detect differences of a large magnitude between family treatment and child only treatment conditions. Greater power will be obtained by randomizing waitlist participants into the two active treatments following the completion of their waiting period.

### Random Allocation Procedure

Randomisation of participants to treatment conditions will be performed by a staff member who is not involved in the recruitment, collection of data or interview procedures. Blocked randomisation is determined using a computer program which generates a list of random numbers and allocation to one of the three conditions. Randomisation will occur immediately following the completion of the baseline interview with the child, with participants informed at this time. Participants will commence their allocated condition one week later.

### Statistical Considerations

Statistical analyses will be performed by a team member who has not been involved in assessing eligibility of participants, allocation of individuals to treatment conditions, administration of treatment, collection of follow-up assessment data or entering of data. Prior to investigating treatment outcome, the three groups will be compared for pre-treatment equivalence on demographic and baseline assessment measures. If significant differences are found, this will be taken into account by including these variables as covariates in outcome analyses. The outcome data will be analysed and reported in terms of statistical significance of differences between groups in change over time on outcome, clinical significance of the change, and effect sizes.

Primary analyses will be undertaken on an intent-to-treat (ITT) basis, including all participants who have been randomized to a condition, regardless of withdrawal from the condition/study. Separate analyses will also be conducted for those who complete treatment. Differences in diagnostic status across groups will be examined using chi-square analyses for each assessment occasion. Continuous data will be analysed using the preferred approach of linear mixed effects modelling, which is able to include participants whose data may be missing at various time points. Other outcomes such as demographic characteristics and reasons for dropout will be described.

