## Methods/Design

### Design of the Trial

This study is designed as a three arm randomised controlled trial with two active interventions ('*child-focused' *and *'family-focused'*) and one comparison (*'waitlist'*) condition. The study will be conducted across 3 hospitals in Australia, The Royal Children's Hospital (RCH) in Brisbane, The Mater Children's Hospital (MCH) in Brisbane and the Women's and Children's Royal Hospital (WCH) Adelaide. There will be six measurement occasions: screening at 1-2 weeks post-hospital admission, baseline, 4-weeks post-baseline, post-intervention, and follow-ups at 6 and 12 months after the post-intervention assessment. A half crossover design will be used to allow baseline and post-test comparisons between the two active treatment conditions and waitlist control group on primary and secondary outcome measures, as well as increasing the sample size for the final evaluation at follow-up. Thus, all children in the waitlist condition will be randomly allocated to one of the two active treatment conditions following their initial waiting period.

This study was granted ethical approval by the University of Queensland Human Research Ethics Committee (protocol number2008002119), the Royal Children's Hospital (Brisbane) Children's Health Service District Ethics Committee (protocol number HREC/09/QRCH/41), The Mater Health Services (Brisbane) Human Research Ethics Committee (protocol number 1305C) and the Children Youth and Women's Health Services (Adelaide) Human Research Ethics Committee (protocol number REC2149/2/2112). The study is funded by an NHMRC Project Grant (569660). The measures to be administered at each time point are listed in Table 1.

**Table 1 T1:** Measures to be administered at each measurement occasion

Measure	Screening	Baseline	4-weeks post-baseline	Post-test	6-month	12-month
Demographics	X	X				
Child Trauma Screening Questionnaire	X	X	X	X	X	X
Heart-rate	X					
Injury severity	X					
Clinician Administered PTSD Scale-Child and Adolescent Version		X	X	X	X	X
Faces Pain Scale		X		X	X	X
Child PTSD Symptom Scale		X	X	X	X	X
Child Depression Inventory-Revised		X		X	X	X
Spence Children's Anxiety Scale		X		X	X	X
Pediatric Quality of Life Scale - Child version		X		X	X	X
Child Behavior Checklist		X		X	X	X
State Trait Anxiety Inventory		X		X	X	X
Pediatric Quality of Life Scale - Parent version		X		X	X	X
Depression, Anxiety and Stress Scale		X		X	X	X
Posttraumatic stress Diagnostic Scale		X	X	X	X	X

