### Primary Outcome Measure

The primary outcome measures will involve an assessment of posttraumatic stress symptoms. Diagnostic status, symptom severity and associated disability/impairment will be assessed using the Clinician Administered PTSD Scale for Children [31].

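### Covariates are selected by testing randomised groups for baseline differences, so chance imbalance sets the adjustment, and the rule cannot be applied to diagnostic status

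*Protocol article*

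**What the plan says.** All of this is in the protocol article. Under Statistical Considerations, before outcomes are examined, "the three groups will be compared for pre-treatment equivalence on demographic and baseline assessment measures". The consequence follows at once: "If significant differences are found, this will be taken into account by including these variables as covariates in outcome analyses". No significance level is given for these tests, and no covariate is named in advance.

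The same section says that outcomes will be reported in terms of "statistical significance of differences between groups in change over time on outcome". It gives two methods. For continuous measures: "Continuous data will be analysed using the preferred approach of linear mixed effects modelling". For diagnosis: "Differences in diagnostic status across groups will be examined using chi-square analyses for each assessment occasion".

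Under Primary Outcome Measure: "Diagnostic status, symptom severity and associated disability/impairment will be assessed using the Clinician Administered PTSD Scale for Children". Diagnostic change is the outcome on which Sample Size and Power Calculations rests. Random Allocation Procedure describes blocked randomisation to three conditions and names no stratification factor.

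**The concern.** When allocation is random, any baseline difference between arms is a chance event. A significance test on it says nothing about whether the variable predicts outcome, which is the property that makes a covariate worth having. Under this rule a strong predictor that falls short of significance is left out, and an irrelevant variable that happens to cross the line goes in. Nobody can say what the primary model is until the baseline data have been tested.

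Two things are at stake. One is precision, because gains available from a known predictor depend on luck. The other is a fixed analysis of the primary outcome. For diagnostic status the rule also fails on its own terms: it promises covariates in outcome analyses, while the named test cannot take any. If an imbalance appeared, the analyst would have to ignore the rule or change the method after seeing it.

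**Working it through.** **Inputs.** From the documents: 140 children, about 45 per arm (Stage 6); about 20% attrition (Sample Size and Power Calculations); 13 rows marked at baseline in Table 1, namely 12 instruments plus demographics. Assumed, because the documents do not give them: a 0.05 two-sided level for the baseline tests, and a correlation r of 0.3 to 0.7 between baseline and later CAPS-CA severity. The plan gives no figure of its own on this point to reproduce.

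**1. How often the rule selects something.** Each variable is selected with probability 0.05, so baseline CAPS-CA becomes a covariate in about 5% of trials.
- Expected number of selected variables: 13 × 0.05 = 0.65.
- Chance of at least one, if independent: 1 − 0.95^13 = 0.487, or 49%.
- Chance of at least one, if the measures are correlated (simulation, three arms of 46, F test): 43% at a correlation of 0.3 and 34% at 0.5.

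Testing several demographic items or subscales would raise these figures.

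**2. How much imbalance passes unadjusted.** The rule compares three groups. For an omnibus F test with 45 per arm, the critical F(2,132) is 3.06. Let two arms differ by D standard deviations.
- Third arm level with one of the two: F = 45·D²/3, so D = √(3 × 3.06/45) = 0.45.
- Third arm midway between them: F = 45·D²/4, so D = √(4 × 3.06/45) = 0.52.

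Pairwise imbalances up to about 0.45 to 0.52 SD can therefore remain non-significant. Imbalance D moves a change-score comparison by (1 − r)·D, against the direction of the imbalance. At r = 0.5 and these upper limits, that is 0.5 × 0.45 = 0.23 SD to 0.5 × 0.52 = 0.26 SD. These are extremes, not typical values.

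**3. Precision.** With unit variance at each occasion, a change score has variance 2(1 − r), and a baseline-adjusted comparison has variance 1 − r². The ratio is (1 + r)/2.

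| Assumed r | Ratio | Cut in variance |
|---|---|---|
| 0.3 | 0.65 | 35% |
| 0.5 | 0.75 | 25% |
| 0.6 | 0.80 | 20% |

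As an illustration, take 37 completers per arm (140 × 0.8/3 = 37.3) and an assumed difference of 0.6 SD. At r = 0.5, power is 73% for change scores and 85% with baseline adjustment.

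**4. Type I error.** The two-step rule was simulated with 37 per arm and 10,000 runs: post-test comparison, adjusted for baseline only if baseline differed significantly. The error was 4.4% at r = 0.5 and 3.6% at r = 0.7.

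The same holds if the default is a change score. In the runs where baseline was selected, the change test rejected 21.9% of the time at r = 0.5 and 13.6% at r = 0.7. Replacing those rejections by an adjusted test at 5% gives:
- r = 0.5: 5 − 5 × 0.219 + 5 × 0.05 = 4.2%
- r = 0.7: 5 − 5 × 0.136 + 5 × 0.05 = 4.6%

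Neither version exceeds 5%.

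**5. Diagnostic status.** Set beside each other, the covariate rule and the chi-square plan do not fit. A chi-square test on the group-by-diagnosis table has no place for a covariate and uses no baseline value.

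**The case against.** Four points can be made for the plan.

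- **Baseline severity is used.** A reader might infer that the baseline CAPS-CA score usually plays no part in the analysis. The documents do not support that for continuous severity. CAPS-CA is measured at baseline, and a mixed model of change over time takes that score as its first occasion. What stands is narrower: adjustment for it as a covariate is not pre-specified, and the chi-square tests ignore it.
- **Selection is shielded from outcomes.** It uses baseline data only, comes before outcomes are examined, and is done by an analyst kept apart from assessment, allocation and treatment. A reader might still infer that false positives are inflated. The simulation shows otherwise: the rule is slightly conservative. This disposes of the bias argument but not of the loss of precision or of a fixed model.
- **The count could be put higher.** Adding heart rate and injury severity gives 15 variables and 54%. Table 1 marks those two at screening only, and the rule concerns demographic and baseline measures, so 13 is the fair count.
- **An analysis plan may settle the covariates.** It may, and silence in an article would be no finding. Here the article states a rule, and the rule as stated is the fault.

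**Conclusion.** The point holds as a fault in a stated rule and should be corrected. It does not threaten the trial's validity. Chance imbalance decides the adjustment set, with a 34% to 49% chance that at least one of 13 variables enters, and the rule cannot be carried out for the outcome on which the trial is powered.

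The loss is one of efficiency and pre-specification. Always adjusting would cut variance by 20% to 35% relative to a simple change-score analysis, for r from 0.6 down to 0.3. These sizes rest on the assumed 0.05 level, on the assumed correlations, and on a change score as a stand-in for the mixed model, whose exact form the article does not give. The selection argument and the conflict with the chi-square test need only randomisation and the plan's own text.

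**What to change.** Delete the sentence that makes covariates depend on significant baseline differences, and report baseline characteristics by arm descriptively, without tests. Then fix the following before outcome data are analysed.

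- **Continuous outcomes:** state either a mixed model with baseline as an occasion and the group means constrained to be equal there, or a mixed model of post-baseline values with the baseline value as covariate. Do not enter the baseline score both as an outcome occasion and as a covariate in the same model. Add a short fixed covariate list, for example hospital and age.
- **Diagnostic status:** use a binary model that accepts covariates, for example logistic regression reported as a marginal risk difference, adjusted for baseline CAPS-CA severity. Keep the chi-square test as an unadjusted supporting analysis.

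The cost is a short rewrite of Statistical Considerations and slightly more analysis work. All the variables named are already collected or known.

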### The role of parents in the treatment of PTSD in children and adolescents

The role of parenting behaviours and parental anxiety have long been recognised as crucial factors in the development and maintenance of childhood anxiety disorders [e.g. [22]]. Recent research also supports the proposal that family-focused CBT results in significantly better long-term outcomes for children with anxiety disorders. For example, Cobham, Dadds, Spence, & McDermott [23] reported that, 3 years after completion of treatment, anxiety-disordered children/adolescents who had received family-focused CBT were significantly more likely to be anxiety diagnosis-free (92%) compared with those who had received child-focused CBT (69%). Increasingly, it is being acknowledged that parental reactions, psychopathology and coping strategies all have the potential to play an important role in the development and maintenance of children's PTSD [e.g. [24,25]].

To date, very few treatment studies in this area have included a parental treatment component, with those that have concluding that a combined parent and child trauma-focused CBT condition results in the best outcomes for children. Although the recent pilot study conducted by Smith et al. [21] did include some degree of parental involvement, this was not quantified and did not appear to be administered in a standardized fashion across participants. From the limited evidence available it is clear that an important direction for future research centres around the question of whether involving parents in treatment significantly enhances child-focused CBT for PTSD.

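### The only test named for diagnostic status, the powered outcome, does not as written deliver the promised intent-to-treat and covariate-adjusted analysis

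*Protocol article*

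**What the plan says.** Primary Outcome Measure lists diagnostic status on the CAPS-CA together with symptom severity and impairment. Sample Size and Power Calculations makes diagnostic status the outcome that sizes the trial: "The study was powered on the comparison between the family-focused versus the child-focused intervention", on diagnostic change, "accounting for an attrition rate of approximately 20" per cent.

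Statistical Considerations then makes four statements that bear on this outcome:

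- The primary analyses are intent-to-treat, "including all participants who have been randomized to a condition, regardless of withdrawal from the condition/study".
- Variables on which the arms differ significantly before treatment enter the outcome analyses as covariates.
- For diagnosis: "Differences in diagnostic status across groups will be examined using chi-square analyses for each assessment occasion".
- For continuous data the method is "linear mixed effects modelling, which is able to include participants whose data may be missing at various time points".

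Only the last method is credited with coping with missing assessments. No rule is given for a child whose diagnosis at an occasion is unknown. Table 1 schedules the CAPS-CA at baseline, 4 weeks, post-test, 6 months and 12 months.

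**The concern.** A chi-square test compares counts of children with and without a diagnosis. A child with no CAPS-CA at that occasion belongs in neither cell. Unless a status is assigned first, the test is an available-case analysis and not the promised analysis of all randomised children. It also has no place for a covariate, so the promised adjustment cannot be made for this outcome even when nothing is missing.

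Dropout could well differ by arm. FF-CBT has 4 parent and 6 child sessions, CF-CBT has 6 sessions, and the waitlist has none for 10 weeks. If children who leave also recover at a different rate from those who stay, the observed proportions no longer estimate the arm effect. The powered comparison could then show a difference where there is none, or hide a real one.

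**Working it through.** **The plan's own figure.** The target is 140 children, and 140/3 = 46.7 per arm. It cannot be reproduced, because alpha, sidedness and target power are not stated. With w = 0.50, an assumed two-sided 5% level and 80% power, a one-degree-of-freedom chi-square needs 32 children in two arms. That is 16 per arm, 48 in three arms, and 48/(1 − 0.20) = 60 after attrition. Varying alpha from 1% to 5%, power from 80% to 95%, the degrees of freedom and the form of inflation gives 47 to 135. This point does not rest on the figure. What matters is that the attrition allowance treats dropouts as lost to the comparison, which is how an observed-case test behaves.

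**How many children the test would use.** At 20% attrition, 140 × 0.80 = 112. In the powered contrast there are 2 × 46.7 ≈ 93 randomised, and 46.7 × 0.80 ≈ 37 observed per arm, so about 74.

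**Possible bias.** Let p be the true remission rate in an arm, d the fraction lost and r the remission rate among those lost. The rate seen in the children who stay is (p − d·r)/(1 − d). Take p = 0.69 in both arms, so that there is no true difference. This is the CF-CBT rate that the Background quotes from the earlier anxiety trial. Assume r = 0.30. The arm-specific losses are also assumed; each pair averages the planned 20%.

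| Loss CF / FF | Observed CF | Observed FF | False difference |
|---|---|---|---|
| 20% / 20% | (0.69 − 0.06)/0.80 = 78.75% | 78.75% | 0 |
| 15% / 25% | (0.69 − 0.045)/0.85 = 75.9% | (0.69 − 0.075)/0.75 = 82.0% | 6 points |
| 10% / 30% | (0.69 − 0.03)/0.90 = 73.3% | (0.69 − 0.09)/0.70 = 85.7% | 12 points |

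Reversing the losses reverses the sign.

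**How much the unstated rule matters.** Take 46 children per arm, 9 missing in each, and observed rates as near to the quoted 92% and 69% as whole children allow. Chi-square without continuity correction:

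| Rule for missing diagnoses | FF-CBT | CF-CBT | Difference | p |
|---|---|---|---|---|
| Observed only | 34/37 | 26/37 | 21.6 points | 0.018 |
| Missing = still diagnosed | 34/46 | 26/46 | 17.4 points | 0.080 |
| Missing = recovered | 43/46 | 35/46 | 17.4 points | 0.020 |

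Assigning the missing children in opposite directions in the two arms gives a range from −2.2 points (34/46 vs 35/46) to +37.0 points (43/46 vs 26/46). With unequal loss (14 missing in FF-CBT, 5 in CF-CBT), observed cases give 29/32 vs 28/41, 22.3 points, p = 0.022. Counting missing children as still diagnosed gives 29/46 vs 28/46, 2.2 points, p = 0.83. Conclusions on either side of 5% are therefore compatible with the wording of the plan.

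**The case against.** The strongest reply is that a chi-square names a test, not an analysis set. The intent-to-treat sentence comes first and governs everything after it, and a chi-square can be run on all randomised children once missing diagnoses have been imputed. A rule for doing so may stand in the full protocol or analysis plan, which a journal article condenses. This part stands. A reader might infer that the plan drops every unassessed child and so contradicts itself outright. The article does not say that.

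Other parts also stand:

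- The bias figures rest on assumed differential loss and assumed remission in dropouts. The article gives only about 20% attrition overall, and the first row of the bias table shows zero. A reader might take the 12 points as an estimate of what will happen; nothing in the article supports that.
- Covariate adjustment is conditional on a significant baseline difference, and the mixed models for continuous outcomes can carry it.
- CAPS-CA severity, analysed as a continuous outcome, would use the repeated scores, so the chi-square affects one component of the primary outcome.
- Multiple imputation and mixed models assume data missing at random. They remove bias only as far as earlier scores predict remission.
- Waitlist children are re-randomised after 10 weeks, so no untreated arm exists at 6 and 12 months. One arm-by-occasion model over all children would ignore this.

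These limits shape the wording and the remedy, but they do not remove the point. An imputation rule alone would not let a chi-square take covariates. The same paragraph credits missing-data handling to the continuous analysis only, and the affected component is the one on which the trial was sized.

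**Conclusion.** The point holds as a mismatch between a stated method and two stated aims. As written, the chi-square cannot carry the covariates at all, and it includes all randomised children only if an imputation step is added that the article does not mention. Without that step, about 74 of 93 children enter the powered contrast at 20% attrition.

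The size of any bias is unknown. It is 6 or 12 points under the assumed losses of 15%/25% or 10%/30% with 30% remission in dropouts, and zero when loss and dropout remission are equal across arms. It would be wrong to conclude that exclusion is planned or that a false FF-CBT benefit is to be expected. The difference between w = 0.50 and the quoted 92% and 69% (w = 0.29 with equal arms) is a separate matter and plays no part here.

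**What to change.** Make the primary analysis of diagnostic status a logistic model adjusted for baseline CAPS-CA severity, in one of two forms:

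- multiple imputation of missing diagnoses using baseline and week-4 CAPS-CA, followed by logistic regression; or
- a longitudinal mixed-effects logistic model.

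Report risk differences with 95% confidence intervals for all three arms at post-test, with the waitlist taken at its 10-week re-assessment. At 6 and 12 months, report FF-CBT versus CF-CBT only, in the children randomised to those arms at baseline. Analyse re-randomised waitlist children separately, or with a term for randomisation stage.

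Because both forms assume missing at random, add a sensitivity analysis that counts missing children as still diagnosed. Keep the chi-square tests as descriptive.

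The cost is analysis-plan wording and a little programming. The measures needed are already scheduled in Table 1, and trial conduct does not change.
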